# A school-based program to prevent depressive symptoms and strengthen well-being among pre-vocational students (Happy Lessons): protocol for a cluster randomized controlled trial and implementation study

**DOI:** 10.1186/s12889-021-12321-3

**Published:** 2022-01-20

**Keywords:** Depression prevention, Well-being promotion, Adolescents, Pre-vocational, School-based intervention, Integrated universal and indicated prevention

## Abstract

**Background:**

Depression is one of the leading causes of illness and disability among young people. In the Netherlands, one in twelve Dutch adolescents has experienced depression in the last 12 months. Pre-vocational students are at higher risk for elevated depressive symptoms. Effective interventions, especially for this risk group, are therefore needed to prevent the onset of depression or mitigate the adverse long-term effects of depression. The aim of this study is to examine the effectiveness and implementation of a school-based program Happy Lessons (HL), that aims to prevent depression and promote well-being among pre-vocational students**.**

**Methods:**

A cluster randomized controlled trial (RCT) with students randomized to HL or to care as usual will be conducted. Pre-vocational students in their first or second year (aged 12 to 14) will participate in the study. Subjects in both conditions will complete assessments at baseline and at 3- and 6-months follow-up. The primary outcome will be depressive symptoms using the Center for Epidemiologic Studies Depression Scale (CES-D) at 6-months follow-up. Secondary outcomes are well-being using the Warwick-Edinburgh Mental Well-Being Scale (WEMWBS) and life satisfaction (Cantril Ladder) measured at 6-months follow-up. Alongside the trial, an implementation study will be conducted to evaluate the implementation of HL, using both quantitative and qualitative methods (interviews, survey, and classroom observations).

**Discussion:**

The results from both the RCT and implementation study will contribute to the limited evidence base on effective school-based interventions for the prevention of depression and promotion of well-being among pre-vocational adolescents. In addition, insights from the implementation study will aid identifying factors relevant for optimizing the future implementation and scale-up of HL to other schools and contexts.

**Trial registration:**

This study was registered on 20 September 2021 in the Dutch Trial Register (NL9732).

**Supplementary Information:**

The online version contains supplementary material available at 10.1186/s12889-021-12321-3.

## Background

Worldwide, depression is one of the leading causes of illness and disability among young people [1]. In the Netherlands, one in twelve adolescents reported experiencing depression in the last 12 months [2]. Adolescent depression contributes to behavioral and educational difficulties such as school absenteeism, poor educational attainment, social problems, substance misuse, and suicidality [3–7]. Depression also has a considerable economic impact in terms of healthcare consumption [8, 9]. In 2017, the costs in the Netherlands that were associated with depression were 1.13 billion euros [10].

Studies show that approximately 50% of adults with a depressive disorder experienced their first depressive episode during childhood or adolescence [11]. The average age among Dutch adolescents for the first episode of depression is 14 years [2]. Mental illness among adolescents tend to persist into adulthood [12]. Accessible, evidence-based interventions aimed at the early detection of symptoms of depression and early intervention are thus crucial to help prevent depression and mitigate the negative long-term effects of depression [13].

In addition to early detection and intervention, improving adolescent well-being is important in mental health promotion [14]. Prior research showed that low levels of well-being are a risk factor for developing depression [15]. Thus, focusing on improving adolescent well-being in general may help reduce the risk of developing depression. Moreover, well-being was found to be associated with a healthier and longer life [16, 17], prosocial behavior, and good relationships with family and friends [16].

Yet, adolescents are typically not inclined to seek help for their mental problems. They have difficulties recognizing problem symptoms, want to solve problems themselves and fear being stigmatized [18, 19]. Providing interventions in social contexts, such as schools, can facilitate getting in touch with hard-to-reach groups, like adolescents. To date, effective school-based programs in the Netherlands that focus both on the prevention of depression and promotion of well-being are scarce and this is especially so for programs targeting the risk group of students in pre-vocational training, who go on to pursue more applied studies in post-secondary vocational education [20]. This is an omission as pre-vocational students are at higher risk for elevated depressive symptoms compared to adolescents in pre-university education [21]. Interventions aimed to improve mental health or well-being of high risk groups are not only scare in the Netherlands, but also internationally [22].

Therefore, effective well-being and depression prevention interventions that are tailored to the needs of these students are needed. This study tries to fill these gaps by examining the effectiveness and implementation of Happy Lessons (HL): a school-based program that focuses on both the prevention of depressive symptoms and the promotion of well-being among pre-vocational adolescents. HL offers an integral and stepped-care approach that combines universal and indicated prevention elements and is delivered by trained mental health professionals within the school context. HL is designed to promote well-being and to identify and detect students that are at risk of developing depression or experiencing depression and facilitate referral to appropriate local mental health and social care services.

The goal of this paper is to describe the protocol for a study that will test the effectiveness of the HL-program in a Dutch adolescent sample of pre-vocational students through a cluster randomized controlled trial (RCT). In addition, an implementation study will be carried out to evaluate the implementation of HL and identify factors that may have influenced implementation.

## Methods

This protocol was developed in accordance with the Standard Protocol Items: Recommendations for Interventional Trials (SPIRIT) statement [23]. See Appendix 1 for the SPIRIT checklist.

### Aim

The main objective of the RCT is to investigate the effectiveness of HL in terms of a reduction of depressive symptoms in pre-vocational students aged 12 to 14 after 6 months compared to care as usual. We hypothesize that adolescents who participate in the HL-program will have lower levels of depressive symptoms at 6-months follow-up than adolescents who do not participate. Secondary outcomes that will be investigated are well-being and life satisfaction. We hypothesize that students who receive HL report higher levels of well-being and life satisfaction than students who do not receive HL.

In addition, we want to identify potential mediator factors that increase or decrease the intervention’s effectiveness. We will investigate school and class climate indicators. We hypothesize that students who receive HL will report higher levels of classmate support, teacher support, and school connectedness, and lower levels of bullying, which will lead to a reduction of depressive symptoms among students.

A secondary aim of this study is to evaluate the implementation process of the HL-program, from the perspectives of intervention recipients, implementers, and the broader stakeholders at the school level (e.g. teachers). The aim of this evaluation will be to understand how the intervention was implemented and what factors might be important when sustaining or expanding the HL-program over time or in new schools.

### Study setting

In the Netherlands, pre-vocational education is a four-year program offering theoretical and practical courses (in Dutch: VMBO). This study will be conducted among first- and second-grade pre-vocational Dutch students. Students in these classes are between 12 and 14 years of age.

### Happy Lessons

#### Theoretical basis

HL is a school-based program designed to prevent depressive symptoms and promote well-being among young people. It is specifically developed for (pre-)vocational students. Prior school-based depression prevention programs have been associated with reduction in depressive symptoms, although effects are typically small [24, 25].

HL contains a unique combination of key elements that can increase program-effects. First, prior research showed that interventions that work well in schools are programs that are shorter in duration, targeted towards high-risk students, and delivered by professionals interventionists instead of classroom teachers [24, 25]. HL is a compact program, focuses on detection elevated depression levels among youth, and is delivered by trained mental health professionals instead of teachers.

Second, mental health prevention programs that combine universal and indicated elements show larger effect sizes [25, 26]. HL meets this criterion as well: it is an integrated approach that combines universal and indicated elements. HL consists of four classical lessons (including two e-learnings), an online screener (called the HL-questionnaire) and an individual advice session for all students in which the at-risk group will be referred to local indicated prevention or treatment.

Third, research shows that ‘positive framing and goal setting’ are important to reduce fear of stigma and encourage active problem solving [27] and that programs with a positive mental health focus are more effective [26]. HL is based on positive psychology and cognitive behavioral therapy, both effective methods in the treatment of depressive symptoms [28–30].

Fourth, for successful implementation, it is important that a program is embedded in the workflow of the stakeholders. Effective implementation is associated with larger effect sizes [26]. The HL-pilots show the program fits in the workflow of the mental health professionals who provide HL. The lessons and advice sessions can be delivered in ‘mentor hours’ at the school, and the HL advice session may be combined with the periodic health screens or ‘adolescent contact moments’ that are conducted by the youth health authorities in the Netherlands. And because of its compactness, HL may be integrated in a bigger lifestyle programs in schools with other lifestyle themes.

Finally, HL is also relevant for the mentally healthy students in the classroom who do not need to improve on depression and well-being outcomes. Should they experience mental health problems in the future, they will have received the message with HL that mental health problems are a normal part of life, that they don't have to feel ashamed, that there are effective skills that can be practiced and that good help is available [31].

#### Program

The program consists of various parts (see Fig. 1): (a) four classroom lessons of which two lessons also contain an e-learning module, (b) an online HL-questionnaire that includes two well-being scales and a depression scale that is administered at the start of the second lesson, (c) an individual consultation session with the mental health professional who delivers HL for each student, and (d) potential aftercare for high-risk students. The program is delivered within approximately 5-8 weeks. The lessons and advice sessions are provided by trained mental health professionals (e.g., prevention workers, called HL-trainers). Teachers are present to support the HL-trainers in providing HL. Before the start of the program, HL-trainers create a personal HL-account for each student in an online database. Students will use the HL-account to gain access to the online HL-questionnaire and e-learning module (lesson 2 and 3).

**Fig. 1 Fig1:**
[figure not shown]
Components of the HL-program

##### The classroom lessons

The first lesson focuses on the introduction of HL and on the subject happiness. The goal of this first lesson is to encourage a discussion about feeling happy or unhappy, familiarize students with different aspects of happiness, discuss the difference between happiness and being lucky, and to break the taboo about feeling unhappy or down. In this context, engaging group assignments and discussions take place.

In the second lesson, students will learn more about the things that might make them happy and the relationship between feelings, thoughts, and actions. In addition to a class-based exercise, students are asked to complete the online HL-questionnaire. This is a questionnaire on demographics (i.e., gender, age), their own health, family situation (i.e., their family’s’ financial situation, and their family members’ (mental) health status), a depression scale, life satisfaction scale, and a well-being scale. After students complete the HL-questionnaire, they will start the e-learning module which contains videos, animations, and fun and engaging exercises. The e-learning module helps students to improve their mood and to practice the skills with their own feelings, thoughts, and actions.

The third lesson starts with an exercise where the HL-trainer describes different situations (e.g., when students receive the results from a test or students have to give a presentation). Students are asked to describe their feelings for each situation (i.e., being angry, sad, scared, or happy). The lesson also contains an e-learning module with the same elements as the second lesson but is focused on: (1) problem solving, (2) communication tips that help students maintain positive relationships with friends, parents, teachers, (3) the importance of helping others, and (4) thinking about their future dreams and how they can achieve these.

The fourth and final lesson includes a recap of what students have learned so far. In addition, it focusses on the relationship between thoughts and feelings and how students can challenge negative thoughts and change them into more helpful thoughts. Students are also asked to fill in a short evaluation questionnaire about the program. The duration of each lesson is approximately 45 minutes.

##### The individual consultation session and potential aftercare

After the final lesson, individual consultation sessions are scheduled with all students. In the online database, the HL-trainer can see the answers of the HL-questionnaire. Based on the answers on the HL-questionnaire, the HL-trainer talks with the student to see if the student needs additional support. Students who report high scores on the HL-questionnaire or report other problems at home/school are offered help by the HL-trainer (i.e., some additional individual sessions) or are referred to appropriate local mental health and/or social care services. This will be done in consultation with the student and their parent(s).

### Design of the RCT

The effectiveness of HL will be tested within a cluster RCT with two conditions: an intervention condition (receiving HL during the study) and a control condition (care as usual, HL will be delivered after the final follow-up assessment). Participating classes will be randomly assigned to either the intervention or the control condition and will be equally distributed across the two conditions within each schoolyear. This design is chosen to avoid a skewed distribution of participants over the two conditions due to school effects. The randomization will be conducted by an independent statistician. Three assessments will be performed in the study: T0 (pre-test, before the start of HL in intervention group); T1 (3-months follow up); T2 (6-months follow-up).

Data will be collected in two cohorts: the first cohort is planned in the 2021-2022 school year and the second cohort is planned in 2022-2023 school year.

See Fig. 2 for the flowchart of the study and Table 1 for an overview of the schedule of enrolment, interventions, and assessment.

**Fig. 2 Fig2:**
[figure not shown]
Flowchart of the study design

**Table 1 Tab1:**
[figure not shown]
Schedule of enrolment, intervention, and assessments

#### Study population

##### Eligibility criteria and recruitment of schools

To provide HL at a school, three different parties need to be involved: schools, mental health organizations that provide the professionals that deliver HL, and – in most cases – the municipality that pays for HL. Schools, mental health organizations, and municipalities were recruited via the website and newsletter of the Trimbos Institute and the HL website. Schools are included in the study if they offer pre-vocational education in at least two first-year or two second-year classes (age 12-14 years). This may also include “combination classes” that contain students from both pre-vocational and higher educational levels.

##### Eligibility criteria of participants

Students are eligible to participate in the study when they meet the following inclusion criteria: enrolment of first- or second-grade students of classes that provide pre-vocational education (including combination classes), informed consent from student and parent(s) and a sufficient knowledge of the Dutch language.

#### Recruitment of participants and informed consent

Two weeks before the start of the study, schools provide information letters and consent forms to parents from both groups (intervention and control condition). In order to give permission for their child’s participation, parents are asked to sign the consent form on paper and send it back to the research team by mail or e-mail within a week. Approximately one week before the start of HL in the intervention condition, a research assistant will visit the participating classes to explain the study and provide an information letter to all students. Students can ask questions and are asked to sign an informed consent form on paper in this recruitment session. Students will be enrolled in HL when they and their parents have both provided consent. In consultation with the school, participating students will receive an incentive (e.g., a voucher).

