#### Sample size

The sample size is based on the main outcome: depressive symptoms in pre-vocational students in first and second year classes. Based on a meta-analysis by Stice et al. [24], we assume an effect size of *d* = 0.20. Thus, we want to test the hypothesis that we will find an effect of *d *= 0.20 (or larger) at 6 months follow-up. This will be tested at a two-sided significance level of 5% and a power of 80%. Accounting for the clustering in the data with 22 students on average per class, an intraclass correlation of 0.02, a cluster size variation of 0.17 and a baseline correlation of 0.30, we need *n* = 315 students in each condition. Furthermore, we expect that approximately 40% of parents and/or students will not provide informed consent. In order to secure the needed sample size, the aim is to sample 525 students per trial. Assuming an average of 4 classes of 22 students per school (divided across intervention and control condition), this will require 48 classes from about 12 schools.

The sample size calculation was performed in Stata version 14.2 statistical software package using the clustersampsi-procedure. The intraclass correlation coefficient (ICC) of 0.02 was based on two studies: the Dutch Health Behaviour in School-aged Children Survey (HBSC) [32], where the ICC on the emotional scale within the Strengths and Difficulties Questionnaire (SDQ) was 0.008 (95% CI: 0.003-0.02) and a large European study where the ICC’s for depressive mood varied across countries from 0.01 to 0.07 [33].

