#### Data collection

Data will be collected through an online questionnaire and students’ self-reports. Students will use their personal HL-accounts (created by the HL-trainer) to gain access to the questionnaires. Data for each assessment and in both conditions will be collected during a regular classroom lesson. At the end of the recruitment session, the research assistant will ask all students to fill in the HL-questionnaire as part of the HL-program. For those participating in the study this data will serve as the baseline measurement (T0) for the RCT. For research purposes, the HL-questionnaire is administered before the start of the HL instead of the second lesson. For the second (T1) and third assessment (T2), teachers are approached to collect and administer the questionnaires in their classes. The duration of each questionnaire will be approximately 15 minutes.

Data collected for research purposes will be stored in a database. For each individual student, a unique respondent number will be used. Students’ names and email addresses will be stored in a separate database, which is only accessible for the data manager of the project.

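### As worded, consent and the baseline questionnaire are obtained when classes are already described as intervention or control, and nothing visible places allocation later or conceals it until then

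*Protocol article*

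**What the plan says.** All references are to the protocol article.

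- **Unit of allocation** (Design of the RCT): "Participating classes will be randomly assigned to either the intervention or the control condition". An independent statistician does this. The section does not say when. Control classes get "care as usual, HL will be delivered after the final follow-up assessment".
- **Parents** (Recruitment of participants and informed consent): two weeks before the start, "schools provide information letters and consent forms to parents from both groups (intervention and control condition".
- **Students** (same section): "Approximately one week before the start of HL in the intervention condition, a research assistant will visit the participating classes to explain the study". They sign consent at that visit.
- **Baseline** (Data collection): at the end of that session "the research assistant will ask all students to fill in the HL-questionnaire as part of the HL-program". For study participants, these answers are the trial's T0.
- **Entry** (Eligibility criteria of participants): students need "informed consent from student and parent(s) and a sufficient knowledge of the Dutch language".
- **Expected refusal** (Sample size): "we expect that approximately 40% of parents and/or students will not provide informed consent". One figure is given, not one per arm.
- **What consent leads to** (Recruitment of participants and informed consent): "Students will be enrolled in HL when they and their parents have both provided consent".

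The Statistical analyses section plans an intention-to-treat mixed model with the baseline score of the outcome as a covariate. Strengths and limitations covers contamination, school self-selection, length of follow-up and self-report, but not recruitment after allocation.

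**The concern.** Randomising classes balances the classes. It balances the enrolled students only if the decision to enrol does not depend on the arm. Here the text speaks of two existing groups when parents are first approached, and it times the student visit by the start of lessons in one of them. If the arm is known at that point, two things can go wrong.

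First, families in HL classes and in waiting classes may consent at different rates or for different reasons. Students who do not consent never enter the analysis set, so intention-to-treat cannot bring them back.

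Second, T0 is a self-report of mood taken in the same session. If students answer it knowing their arm, the covariate meant to deal with baseline imbalance is itself affected.

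The planned effect is small, d = 0.20, so a modest bias is a sizeable share of it, and recruiting more students does not reduce it.

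Separately, the Recruitment and Data collection sections differ on what consent governs. One ties entry into HL to consent. The other has all students answer the questionnaire as part of HL, with only some of them in the study.

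**Working it through.** **1. The plan's own figure.** Sample size gives n = 315 per condition and 40% non-consent: 315 / (1 − 0.40) = 525. This reproduces the stated 525, read as per condition. The class count agrees: 48 × 22 = 1,056 students, or 528 per condition, of whom 528 × 0.60 = 316.8 would consent. In total 2 × 525 = 1,050 are approached and 1,050 × 0.40 = 420 are expected to stay outside the trial. The sample size does not change under this point; the issue is bias.

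**2. Order of events.** Setting the sections side by side:

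| Step | Timing given | Arm mentioned? |
|---|---|---|
| Randomisation of classes | none | – |
| Parent letters and forms | two weeks before the study starts | both groups named |
| Student information and consent | about one week before HL starts | timed by the intervention condition |
| T0 | end of the same session | – |

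The natural reading is that the groups exist by the second row. No sentence says so outright, and none says the reverse.

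**3. Illustration of size (assumed inputs, not in the documents).** Suppose 65% consent in HL classes and 55% in control classes, and the extra 10 points differ from the other consenters by g SD on the 6-month CES-D.

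Bias = (0.65 − 0.55) / 0.65 × g = 0.154 × g

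- g = 0.3: 0.046 SD, and 0.046 / 0.20 = 23% of the target effect.
- g = 0.5: 0.077 SD, and 0.077 / 0.20 = 38%.

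**4. A second model (also assumed).** Let 60% consent in both arms, with consent correlated ρ with the outcome in one arm only. The mean shift is ρ × φ(0.253) / 0.60 = 0.644ρ. At ρ = 0.05 this is 0.03 SD (16% of 0.20). At ρ = 0.10 it is 0.06 SD (32%). At ρ = 0.20 it is 0.13 SD (64%). Equal consent rates therefore do not by themselves rule out bias.

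**5. What baseline adjustment does.** The plan assumes a baseline correlation of 0.30. The result depends on how selection works.

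- *Through baseline CES-D only, accurately measured.* A 0.3 SD gap at T0 implies 0.3 × 0.30 = 0.09 SD at follow-up. The unadjusted bias is 0.154 × 0.09 = 0.014 SD, 7% of the target, and adjustment removes it.
- *Through factors tied to the later outcome itself.* Adjustment removes about 0.30² = 9%: 0.046 × (1 − 0.09) = 0.042 SD remains.
- *T0 answers shifted by knowing the arm.* A shift of δ SD in one arm's T0 enters the adjusted contrast as about 0.30δ with the opposite sign. Adjustment then introduces error.

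**The case against.** The strongest reply is that the order is a reading, not a statement. Naming both groups could mean only that the same procedure applies in each, written from the planner's side. The flowchart and the schedule of enrolment would show the sequence, and neither is visible. A journal article may also leave the timing and concealment of allocation to the full protocol. This stands, and it is why the point is limited to what the text permits. It does not dispose of the point, because the article does more than stay silent: it describes recruitment in terms of existing groups.

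Three stronger readings are tempting and not supported:

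- *Families are told their arm.* No sentence says that the letters differ or reveal it. The text describes one letter procedure and one class visit, which fits a concealed process equally well.
- *Consent buys immediate HL in one arm and delayed HL in the other, so refusal must differ.* This rests on the sentence that ties HL entry to consent, which the Data collection section contradicts. A sentence in dispute cannot also serve as evidence of a differential incentive.
- *Baseline adjustment removes little of any bias.* This fails where selection runs through current symptoms, as step 5 shows. The planned sensitivity analysis also adds gender, age, immigration background, well-being and life satisfaction. What remains is selection on unmeasured factors, and a T0 affected by knowledge of the arm.

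It is also fair that the consent split and the SD gaps are assumed, and that late release of allocation burdens the outside organisations that supply trainers.

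**Conclusion.** The point holds in a conditional form. As worded, the plan allows enrolment and T0 to depend on the arm, and no visible sentence prevents it. Whether bias would arise depends on two things the documents do not settle: that allocation precedes consent and T0, and that parents, students or the research assistant know it. If both are true, intention-to-treat gives no protection and baseline adjustment gives partial protection.

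The size cannot be estimated from the documents. Under the assumed 65%/55% split it runs from 0.014 SD before adjustment (about nil after it), when a 0.3 SD gap acts through baseline CES-D alone, to 0.046–0.077 SD when the extra consenters differ by 0.3–0.5 SD on the outcome itself, against d = 0.20.

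The conflict over what consent governs stands whatever the order of randomisation. The point should be acted on because the remedy is cheap and the bias could not be repaired in the analysis.

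**What to change.** - **Timing.** State when classes are randomised relative to consent and T0. Have the independent statistician release each school's allocation only after its consent forms and T0 questionnaires are in.
- **Fallback.** If trainer scheduling prevents this, disclose the allocation only to the school planner. Keep parents, students and the research assistant unaware until T0 is complete, and use one identical letter for both groups.
- **Reporting.** Give the numbers approached and consenting by arm, and compare characteristics held by the school, such as educational level, across arms.
- **Wording.** Reconcile the Recruitment sentence that links HL entry to consent with the Data collection text, in which all students answer the questionnaire as part of HL and only some are in the study.

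If allocation is already concealed until T0, one sentence saying so answers the first two items. Otherwise the cost is a re-ordering of existing steps. The sample size and the analysis model are unchanged. The real downside is logistical: schools and HL-trainers would have about a week's notice of which classes start, or would have to book provisionally.
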